#### Concealment mechanism {16b}

The allocation sequence is completely concealed from all study personnel.

#### Implementation {16c}

The project leader will assign participants to interventions.

### Assignment of interventions: blinding

#### Who will be blinded {17a}

The therapists and the participants in the trial cannot be blinded to treatment allocation due to the complex nature of the treatment, but group allocation will be masked to the assessors up to completion of the 12-month follow-up. Participants will receive explicit instructions not to discuss their treatment allocation with the assessor. If a participant still unintentionally discloses their treatment allocation, another blind assessor will reassess the diagnosis and symptom severity using recordings of the CAPS-5 interviews. The participant will also be assigned another assessor at subsequent follow-ups. After each assessment, the assessors will be asked to guess the participants’ allocation, and answers will be compared to chance at the end of the study to measure blinding integrity. Data managers, primary outcome assessors and trial statisticians will be blinded to group allocation until the final data analyses are completed.

#### Procedure for unblinding if needed {17b}

Emergency unblinding will be implemented when deemed clinically necessary, for example, in situations where treatment decisions demand knowledge of the allocated intervention or when there is an unexpected occurrence of a serious adverse event.

### Data collection and management

#### Plans for assessment and collection of outcomes {18a}

Participants will complete baseline assessments, measures at each individual treatment session, immediately after treatment completion and at the 1-month, 6-month, and 12-month follow-ups. All data are collected in BASS, a secure digital platform developed by Karolinska Institutet.

#### Plans to promote participant retention and complete follow-up {18b}

The digital platform is equipped to send out automatic reminders if assessments are overdue. The assessors will contact participants who cancel or do not show up at appointments by phone, and if no contact is made, send the participant a letter according to established clinical routines.

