### Sample size {14}

A power calculation was conducted to determine the number of participants needed to evaluate intensive treatment compared to weekly delivered sessions. The power analysis for the trial is based on the CAPS-5, where a significant difference in treatment effects between groups would be set to at least 10 points. With an estimated standard deviation of the CAPS-5 of 20, this represents a standardized mean difference in terms of Cohen’s *d* of 0.5 [24]. Given 95% power, 10% data attrition rate, and an alpha level of 0.05, we estimate that we would need a total of 140 participants to find a statistically significant moderate between-group effect of *d* = 0.5 at our primary endpoint (1 month). We also conducted a power analysis to ensure that we would be able to detect our expected differences in dropout rate, a reduction in the dropout rate from a 22% baseline rate to 5% in the intervention group with conditional linear regression, conditional on the four randomization strata arising from the combination of sex (male, female) and trauma onset (childhood, adulthood). The power was estimated with 1000 randomly generated datasets. The following table shows the estimated power with different sample sizes (*n*).

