### Data management {19}

Participants will complete online questionnaires through the online platform BASS, hosted on Karolinska Institute’s secure computing facilities, with data backup handled by the same institute. The platform ensures additional security through two-factor authentication. The digital data, including audio files, are stored on encrypted servers, requiring a VPN connection, a personal service card, and/or two-step authentication in accordance with local data management guidelines. The analog data gathered during the study are securely stored within a locked file cabinet. Access to this cabinet is limited to the principal investigator and the study coordinator, who hold the key. Additionally, entry to the archive room corridor necessitates a personal service card, and access to the room itself requires a passcode. This ensures the protection of the data’s confidentiality and integrity.

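### Masked CAPS-5 assessors are given the job of chasing missed assessments, an avoidable contact before the rating that the disclosure safeguards only partly cover

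*Protocol article*

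**What the plan says.** The section on retention and complete follow-up {18b} assigns the contact after a cancelled or missed appointment: "The assessors will contact participants who cancel or do not show up at appointments by phone", then by letter if they cannot be reached. The section on adherence to interventions {11c} gives the parallel task for treatment appointments to the therapist. Section {18b} is therefore best read as being about assessment appointments.

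The blinding section {17a} says "group allocation will be masked to the assessors up to completion of the 12-month follow-up". It provides four safeguards:

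- **Instruction:** "Participants will receive explicit instructions not to discuss their treatment allocation with the assessor".
- **Re-rating:** after an unintentional disclosure, "another blind assessor will reassess the diagnosis and symptom severity using recordings of the CAPS-5 interviews".
- **Change of assessor:** "The participant will also be assigned another assessor at subsequent follow-ups".
- **Check:** "After each assessment, the assessors will be asked to guess the participants’ allocation", and the guesses are tested against chance when the study ends.

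Table 3 places CAPS-5 at enrollment and at 1, 6 and 12 months after treatment, with 1 month as the primary endpoint. The sample size section {14} plans for "a reduction in the dropout rate from a 22% baseline rate to 5% in the intervention group".

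**The concern.** Participants and therapists know the treatment arm, so the validity of the clinician-rated primary outcome rests on the assessor not knowing it. A call about a missed visit can easily turn to how treatment went or whether the person stopped. The two formats are easy to tell apart from a passing remark: one is an intensive week plus three boosters, the other is 15 weekly sessions.

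Treatment dropouts are encouraged to attend all outcome assessments (Treatment variables), and the models are to use every available observation {20c}. If participants who left treatment are among those who need a call, their ratings count in the primary comparison. An assessor who has learned the arm, or something that points to it, may rate differently. The call adds a route to that knowledge which the trial does not need, because arranging an appointment requires no skill in rating PTSD.

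**Working it through.** The protocol states no figure on this point, so the main check is to set the sections side by side.

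**Step 1: who calls, and when.** Section {18b} names the assessors. Section {11c} gives missed treatment sessions to the therapist. Table 3 has no CAPS-5 visit during treatment, and the enrollment CAPS-5 precedes allocation. The calls that matter are therefore those about the 1-, 6- and 12-month visits. A call to rebook a visit normally precedes the rating at that visit.

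**Step 2: each safeguard in {17a} applied to a disclosure in such a call.**

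| Safeguard | Does it reach a call before the interview? | What is left |
|---|---|---|
| Instruction to participants | Yes; it is not tied to the interview | It concerns allocation; having stopped treatment is a different fact and can still come out |
| Re-rating | Yes; the trigger names no setting | The second rater works from an interview that an unmasked assessor may have led |
| New assessor | Only from the next follow-up | A disclosure before the 1-month visit is remedied after the primary endpoint |
| Allocation guess | Partly | It can detect unmasking but cannot prevent it |

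The gap is narrow: nothing says that a different assessor conducts the interview that follows the disclosure.

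**Step 3: what dropout status alone would tell an assessor.** The inputs are the planning dropout rates in {14}, 22% for weekly PE and 5% for iPE, and 1:1 allocation. By Bayes' rule with equal arms:

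P(weekly PE | left treatment) = 0.22 / (0.22 + 0.05) = 0.22 / 0.27 = 0.815, or about 81%.

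Without that knowledge the probability is 50%. Learning that someone left treatment would partly unmask the assessor even if the arm were never mentioned. The figure applies to a person known to have left treatment, not to everyone who misses an assessment.

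**Step 4: effect on the CAPS-5 contrast.** This would need the share of each arm that misses an assessment, the share of those who disclose, the share not remedied by re-rating, and the size and sign of the rating shift. The documents give none of these, so no effect in points can be derived.

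**The case against.** The strongest reply is that nothing here is an error. Giving assessors a logistic task is compatible with masking them. The instruction in {17a} is general enough to cover a telephone call, the re-rating rule is triggered by any unintentional disclosure, and the Challenges section says that routines to improve blinding integrity will be developed. CAPS-5 visits fall after treatment, and a participant could equally reveal something in the interview itself. Much of this stands: the risk is reduced, and the documents do not contradict themselves. It does not dispose of the point, because {18b} makes an explicit assignment rather than leaving a detail out, and the safeguards do not settle who conducts the interview after an early disclosure.

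Several stronger readings are tempting and not supported:

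- **The calls are unrecorded.** The protocol does not say whether they are recorded or logged.
- **The caller is also that participant's rater.** Section {18b} speaks only of the assessors as a group.
- **Assessor masking is the trial's only masking.** Section {17a} also blinds data managers and trial statisticians.
- **Those who need a call are mostly treatment dropouts.** This is plausible but not documented; missing an assessment and leaving treatment are different events.
- **The bias can be put in points.** Suppose, purely as an assumption, that 20% of weekly PE and 5% of iPE participants are called and disclose, and that ratings shift by 2 to 5 points in the same direction. The contrast then moves by (0.20 − 0.05) × 2 = 0.3 to (0.20 − 0.05) × 5 = 0.75 points, against a 10-point target. Those shares are close to the whole planned dropout (22% and 5%) and ignore re-rating. If the shifts ran in opposite directions by arm, the result would be (0.20 + 0.05) × 2 = 0.5 to (0.20 + 0.05) × 5 = 1.25. The answer depends entirely on what is assumed.

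**Conclusion.** The point holds as a minor, avoidable weakness in the masking procedure. Masked assessors are assigned a contact that normally precedes the rating, and the existing safeguards reduce the risk of unmasking without removing it. The gap that remains is an interview led by an assessor who already knows the arm, with a replacement only at later visits.

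Neither the size nor the direction of any bias can be computed from the documents. The one figure that follows from them is the 81% probability of weekly PE for a person known to have left treatment. It rests on the planning dropout rates being realised and on 1:1 allocation. A reader might infer that the primary comparison is materially biased or that the protocol contradicts itself; the documents support neither. The case for acting is that the risk is needless and the remedy costs little.

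**What to change.** Reword {18b} so that existing non-assessor staff make the calls, letters and rebookings for missed assessments and do not pass reasons for cancellation to the assessor. The documents already mention a study coordinator (Data management {19}: "Access to this cabinet is limited to the principal investigator and the study coordinator") and a team for recruitment and daily administration {5d}. They do not show how much spare capacity these roles have.

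Add one sentence to {17a}: if an assessor learns the allocation before an interview, another masked assessor conducts that interview.

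The first change costs a little coordinator or administrative time and leaves the retention effort unchanged. The second draws on another assessor only when a disclosure occurs, and {17a} already relies on a second assessor for re-rating. With the last follow-up expected in October 2026 (Trial status), the change protects whichever assessments are still to come when it is made.

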### Data management {19}

Participants will complete online questionnaires through the online platform BASS, hosted on Karolinska Institute’s secure computing facilities, with data backup handled by the same institute. The platform ensures additional security through two-factor authentication. The digital data, including audio files, are stored on encrypted servers, requiring a VPN connection, a personal service card, and/or two-step authentication in accordance with local data management guidelines. The analog data gathered during the study are securely stored within a locked file cabinet. Access to this cabinet is limited to the principal investigator and the study coordinator, who hold the key. Additionally, entry to the archive room corridor necessitates a personal service card, and access to the room itself requires a passcode. This ensures the protection of the data’s confidentiality and integrity.

### Confidentiality {27}

The data collected in the study will be handled and stored in accordance with the Research Data Management Policy of Karolinska Institutet and Stockholm County and in compliance with both Swedish and European legislation. All study personnel involved in the trial are obligated to uphold confidentiality principles in their capacity as healthcare system employees.

### Plans for collection, laboratory evaluation, and storage of biological specimens for genetic or molecular analysis in this trial/future use {33}

See above 26b there will be no biological specimens collected.

### Statistical methods

#### Statistical methods for primary and secondary outcomes {20a}

The data analytic plan is uploaded in a separate file at the OSF https://osf.io/7qsb3. The data analyses will be carried out by an independent statistician who is not part of the research group. This statistician will also remain blind to the group allocation throughout the duration of the trial.

#### Interim analyses {21b}

No interim analysis is planned within this trial.

#### Methods for additional analyses (e.g., subgroup analyses) {20b}

To detect differences in treatment effects by gender, we will analyze the interaction between treatment arm and gender. Between- and within-group moderation tests will also be performed based on baseline characteristics such as PTSD and complex PTSD symptom severity, type of trauma, comorbidity, level of threat during the traumatic event, educational level, occupational status, comorbidity factors, disturbances in self-organization, perceived working alliance, and treatment credibility. Mediators of treatment outcome to be considered are avoidance behavior and negative cognitions on the CAPS-5 and PCL-5 and change in emotional responding (SUD-ratings).

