The research questions to be answered within the project are as follows:Is iPE more efficacious than weekly delivered sessions of prolonged exposure regarding reduction of blinded assessor rated PTSD symptom severity 1-month posttreatment in each respective treatment arm?Is iPE more cost-effective than weekly delivered sessions of prolonged exposure at 1 month, 6 months, and 12 months posttreatment?Does iPE lead to less dropout than weekly delivered sessions of prolonged exposure up to 1 month posttreatment?Does iPE lead to more adverse events than weekly delivered sessions of prolonged exposure up to 12 months posttreatment?Does iPE lead to a faster recovery rate than weekly delivered sessions of prolonged exposure up to 12 months posttreatment?Is iPE more efficacious than weekly delivered sessions of prolonged exposure regarding the reduction of self-rated depression and increased quality of life at 1 month, 6 months, and 12 months posttreatment?What is the mechanism of change of prolonged exposure? Does the mechanism of change in iPE and weekly delivered sessions differ?What are the moderators of the treatment effect?Are the therapeutic gains of iPE maintained at long-term follow-up (6 and 12 months after treatment)?

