**Self-rated instruments**									
PCL-5^a^			X	X	X	X	X	X	X
ITQ^a^			X	X	X	X	X	X	X
PHQ-9^b^			X		X	X	X	X	X
EQ-5D^b^			X		X	X	X	X	X
AQoL-6D^b^			X		X	X	X	X	X
TIC-P^b^			X		X	X	X	X	X
NEQ^b^					X	X	X	X	X
CEQ^c^				X					
WAI-SR^d^				X					
Treatment preference	X						X		
SUD-ratings^e^				X	X				

*Abbreviations*: *AQoL-6D* Assessing Quality of Life 6 Dimensions, *CAPS-5* Clinician-Administered PTSD Scale for DSM-5, *CEQ* Credibility/Expectancy Questionnaire, *ITQ* The International Trauma Questionnaire, *MINI* Mini International Neuropsychiatric Interview, *NEQ* Negative Effects Questionnaire, *SUD* Subjective Units of Distress Scale, *TIC-P* Treatment Inventory of Costs in Psychiatric Patients, *PHQ-9* Patient Health Questionnaire, *WAI-SR* Working Alliance Inventory–Short Form Revised

^a^PCL-5 and ITQ are administered daily during the intensive phase of treatment in the I-PE group

^b^PHQ-9, EQ-5D, AqoL-6D, TIC-P, and NEQ are administered immediately after treatment completion, w5 in the I-PE arm and w15 in the weekly delivered PE arm

^c^CEQ is administered after the first individual session in each treatment format

^d^WAI-SR is administered at the third individual session in each treatment format

^e^SUD-ratings are collected each individual treatment session

The primary outcome measure is the gold-standard clinical interview CAPS-5 that assesses PTSD symptom severity and past month diagnosis of PTSD [11] administered at enrollment, 1 month after treatment completion (primary endpoint), and at 6- and 12-month follow-ups. The CAPS-5 total severity score has high internal consistency (Cronbach’s *α* = 0.88) and interrater reliability (intraclass correlation coefficient = 0.91) and good test–retest reliability (intraclass correlation coefficient = 0.78) [11]. In this study, treatment response will be deemed successful if there is a minimum improvement of 10 points on the CAPS-5 scale between baseline and the participant’s last recorded measurement within the baseline to 12-month follow-up period. Remission will be defined as the absence of a PTSD diagnosis and/or a CAPS-5 total symptom severity score below 24, following the criteria set by Blevins et al. [12]. To be categorized as having achieved recovery, participants must maintain their remission status through the subsequent follow-up assessment.

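### Alliance and credibility are listed as baseline moderators but measured during treatment, and CAPS-5 clusters listed as mediators have no measurement before the 1-month CAPS-5 endpoint

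*Protocol article*

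**What the plan says.** Objectives {7} poses two relevant research questions: "What is the mechanism of change of prolonged exposure" (and whether it differs by arm), and "What are the moderators of the treatment effect".

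Methods for additional analyses {20b} says how they will be approached. On moderators: "Between- and within-group moderation tests will also be performed based on baseline characteristics such as PTSD and complex PTSD symptom severity". The list that follows ends with "disturbances in self-organization, perceived working alliance, and treatment credibility". On mediators: "Mediators of treatment outcome to be considered are avoidance behavior and negative cognitions on the CAPS-5 and PCL-5", with change in SUD ratings as a further candidate.

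The timing is given elsewhere. Sequence generation {16a} places randomisation after the baseline assessment. Table 3 has no baseline entry for the credibility questionnaire (CEQ) or the alliance inventory (WAI-SR). Its footnotes read "CEQ is administered after the first individual session in each treatment format" and "WAI-SR is administered at the third individual session in each treatment format". Outcomes {12} says the CAPS-5 is "administered at enrollment, 1 month after treatment completion (primary endpoint), and at 6- and 12-month follow-ups". Table 3 shows the PCL-5 at baseline, through the treatment weeks, at posttreatment and at every follow-up. SUD ratings are taken at each individual session.

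**The concern.** A test of baseline moderation asks whether the arm difference varies with something fixed before allocation. If the arm can change the variable, or the variable is read at a different point of treatment in each arm, the interaction mixes effect modification with the effect of treatment on the variable. The comparison within levels of that variable is then no longer protected by randomisation.

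A mediator has to change before the outcome and be distinct from it. If it is a component of the outcome score taken at the same visit, the indirect effect is partly arithmetic and has no time order. The trial could then report a mechanism that its data cannot distinguish from a general fall in symptoms.

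Both matters are named research questions. Neither touches the primary comparison of the arms.

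**Working it through.** The article states no figure for these analyses, so there is none to reproduce. The check sets each listed variable against its measurement time and then illustrates the size of the mediator problem.

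**Moderators.** After gender, which has its own interaction test, the list has 11 entries if PTSD and complex PTSD severity are counted separately and comorbidity is counted twice, as written. Nine are pre-treatment characteristics or are measured at enrolment or baseline. The other two are not:

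| Variable | iPE (Table 2) | Weekly PE (intervention description) |
|---|---|---|
| CEQ, after individual session 1 | Monday, after the group rationale and the first imaginal exposure | Week 1, after rationale, choice of index trauma and breathing retraining; no imaginal exposure yet |
| WAI-SR, at individual session 3 | Tuesday 14:00 (day 2), third imaginal exposure | Week 3, first imaginal exposure |

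Both follow randomisation and the start of treatment. At each reading the two arms have had different content and different elapsed time.

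**Mediators.** There is no CAPS-5 value between enrolment and the 1-month endpoint. For that endpoint, the only post-randomisation CAPS-5 avoidance or cognition score available in time comes from the interview that gives the outcome. PCL-5 and SUD values from the treatment period precede the endpoint and are not part of the CAPS-5 score.

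**Size of the same-interview problem.** Inputs:
- Cronbach's alpha of the CAPS-5 total, 0.88 (Outcomes {12}).
- Share f of CAPS-5 items in the mediator. The article gives no item counts, so f is assumed, from 0.10 to 0.45.
- Assumed model: parallel items, with treatment shifting every item equally, so there is no specific mechanism.

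The apparent mediated share of the effect on the total is f / (1 − (1 − f) × 0.88):

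- f = 0.10: 0.10 / 0.208 = 48%
- f = 0.20: 0.20 / 0.296 = 68%
- f = 0.35: 0.35 / 0.428 = 82%
- f = 0.45: 0.45 / 0.516 = 87%

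Under this model the mediator's own items account for only the fraction f of the total effect, so the excess is spurious.

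If the shared items are removed from the outcome but the visit stays the same, each share is multiplied by 0.88. That gives 42%, 60%, 72% and 77%. Most of the distortion therefore comes from measuring both at the same time, and removing items alone does not cure it.

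A simulation used 20 items (assumed), 126 participants analysed (140 × 0.9), a true effect of d = 0.5 and 3000 runs. It gave shares of 48%, 82% and 87% for f = 0.10, 0.35 and 0.45. Both paths were significant in about 49%, 70% and 74% of runs respectively.

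**The case against.** A reader might infer that the mechanism and moderator questions cannot be answered at all. The article does not support that. Only two of the 11 listed moderators are affected, and the gender interaction is untouched. The mediator sentence also names the PCL-5 and SUD ratings, both collected during treatment and so in the right order for the 1-month CAPS-5.

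A reader might also infer that a CAPS-5 cluster will appear as a significant mediator whenever treatment reduces symptoms. That does not follow from part-whole overlap. In the simulation it happened in about half to three quarters of runs, which is often but not always.

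Three further points can be made for the plan:

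- **The model is left to the separate analysis plan.** {20b} speaks of mediators to be considered and does not pair a 1-month cluster with the 1-month total. This stands in part. Clusters at 1 month could precede 6- or 12-month outcomes, although the constructs still overlap. For the primary endpoint, however, no model can supply a CAPS-5 measurement that is not taken.
- **Within-group tests are also planned.** Early alliance or credibility as a predictor of outcome within one arm does not condition the randomised contrast. This stands. The fault lies in the baseline label and the between-arm interaction, not in every use of these variables.
- **These are additional analyses.** True, and it limits the weight of the point. But the article relies on prospective registration of its hypotheses and analysis plan, so the variable lists should be usable as written.

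**Conclusion.** The point holds in two limited parts.

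First, working alliance and credibility are wrongly classed as baseline characteristics. They are measured after randomisation and after treatment starts, at stages that are not comparable between arms. A between-arm interaction with either does not estimate baseline effect modification. This rests only on the article's own timing and needs no assumption.

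Second, CAPS-5 avoidance and negative cognitions cannot serve as mediators of the 1-month CAPS-5 endpoint, because they would be parts of that score from the same interview. The absence of an earlier measurement is a matter of the schedule. The size of the distortion, an apparent mediated share of 48% to 87% with no specific mechanism, is illustrative. It depends on the parallel-item model, the assumed item shares and the quoted alpha applying within this sample. It does not apply to PCL-5 or SUD measures taken during treatment.

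The primary analysis is unaffected.

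**What to change.** In {20b}, and in the analysis plan if it repeats the list:

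1. Remove WAI-SR and CEQ from the between-arm baseline moderators. Analyse them as post-randomisation process variables or as predictors within each arm.
2. State that CAPS-5 clusters will not be used as mediators of the 1-month CAPS-5 outcome.
3. For that endpoint, use PCL-5 avoidance and cognition items and SUD ratings taken during treatment, before the outcome.
4. Where mediator and outcome come from the same scale (for example a PCL-5 cluster and a later PCL-5 total), exclude the mediator's items from the outcome score. This is unnecessary when a PCL-5 or SUD mediator is paired with the CAPS-5.

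The cost is two between-arm moderator tests and the CAPS-5 mediators at the primary endpoint. No new data are needed. Collecting credibility before allocation would make it a true baseline variable, but Trial status gives September 2023 as the start of inclusion, so participants already randomised could not supply it. The change of wording is the practical route.
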